#### **● Serious Adverse Events**

An SAE for this study is any untoward medical occurrence that is believed by the investigators to be causally related to treatment of the clinical trial and results in any of the following:

- (1) Results in death
- (2) Life-threatening, meaning the subject is at risk of death at the time of event.
- (3) Requires hospitalization or prolongation of existing hospitalization. Emergency room visits that do not result in admission to the hospital should not be considered as a serious adverse event of requiring hospitalization or prolongation of existing hospitalization, and such emergency room visits should be evaluated for one of the other serious outcomes instead.
- (4) Results in disability/incapacity.

(5) Is a congenital anomaly/birth defect.

(6) Events requiring medical and/or surgical intervention to prevent one of the other outcomes listed in the definition above or, based on medical and/or scientific judgment of investigator, are important and should be considered serious.

- **Disease-related Event**

The disease-related event is defined as an event that can be explained by the nature cause of KD, including eye redness, skin rash, and desquamation. The disease-related events and conditions are usually recorded according to the protocol and should not be considered as an AE. For those events that the investigator considers to be more severe than expected, should be reported as AEs or SAEs as appropriate. For all events that result in death or are life-threatening, must be reported SAEs.

- **Reporting and Recording of AE and SAE**

All AEs occurring after entry into the study and until hospital discharge will be recorded. All AEs and SAEs should be documented in the source documents and the relevant CRF and SAE form when applicable. The investigator may be asked to provide photocopies of the medical records for completing the AE or SAE report. It is the responsibility of the investigator to report AEs or SAEs by diagnosis terminologies, if possible. The investigator will be asked to determine the severity and causality of each AE and SAE based on the CTCAE version 4.03 and investigator's clinical judgment.

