The risk of aspirin therapy in children with KD is considered to be low and appear to be similar to those reported in other settings. However, serious aspirin side effects have been reported in children treated for KD, including hepatic toxicity, gastritis, upper gastrointestinal bleeding, sensorineural hearing loss, and rarely, Reye’s syndrome.[19-22] Considering the risks of drug toxicity and the lack of evidence for preventing CAL formation, the role of high-dose aspirin in the acute phase of KD needs to be reassessed. Therefore, we initiate this multi-center, prospective, parallel-group, open-label, non-

inferiority RCT to investigate whether high-dose aspirin in the acute stage of KD has beneficial effects on the prevention of CAL formation.

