## **Withdraw criteria**

Participants should be withdrawn from the clinical trial if any of the conditions set below has occurred. The reason for a patient withdrawn from the study will be recorded in the case report form (CRF) and in the participant's medical record.

1. Participant or his/her legal guardian decides to withdraw his/her ICF.
2. Participant has allergic reaction during IVIG or aspirin treatment.
3. Participant develops AE or SAE that the investigator considered a cessation of the study treatment is necessary.
4. Participant is lost of follow up.
5. Investigator considers that the participant is no longer physically and/or psychologically feasible to remain in the study.

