### **3.9 Blinding**

Participants and study investigators are unblinded to the group of IVIG alone or IVIG plus high-dose aspirin.

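### Section 3.12 keeps events that Kawasaki disease could explain, including skin rash, out of the AE record on unblinded judgement, with no test of onset or of drug cause

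*Combined protocol and SAP*

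**What the plan says.** The Disease-related Event paragraph of section 3.12 has four parts.

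- Definition: "The disease-related event is defined as an event that can be explained by the nature cause of KD, including eye redness, skin rash, and desquamation".
- Consequence: "The disease-related events and conditions are usually recorded according to the protocol and should not be considered as an AE".
- First exception: "For those events that the investigator considers to be more severe than expected, should be reported as AEs or SAEs as appropriate".
- Second exception: "For all events that result in death or are life-threatening, must be reported SAEs".

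The Adverse Events paragraph of the same section defines an AE as any untoward occurrence during participation, whether or not a causal link is possible, and includes worsening of existing disease.

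Section 3.9 states: "Participants and study investigators are unblinded to the group". Section 2.2 makes the comparison of AEs and SAEs between arms a secondary objective. The second withdrawal criterion in section 3.2 reads: "Participant has allergic reaction during IVIG or aspirin treatment". Section 2.1 describes serious aspirin side effects reported in children treated for Kawasaki disease (KD), "including hepatic toxicity, gastritis, upper gastrointestinal bleeding, sensorineural hearing loss", and rarely Reye's syndrome.

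**The concern.** The two paragraphs of section 3.12 give opposite instructions. The AE definition sets cause aside, while the disease-related rule removes an event because of its presumed cause. The threshold for removal is low: it is enough that KD could account for the event. Nothing requires the sign to have been there before dosing, and nothing asks whether IVIG or aspirin is an equally good explanation.

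Skin rash shows the problem. It is an entry criterion for KD and one of the three named non-AEs, but it can also be how an allergic reaction appears. A rash that starts after the first dose can therefore be filed as disease and left out of the AE table, in full compliance with the protocol.

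The AE comparison is a stated objective, and drug toxicity is one of the reasons section 2.1 gives for reassessing high-dose aspirin. If both arms lose events at the same rate, the comparison loses power. If the arms lose them at different rates, a difference can be hidden or created.

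**Working it through.** **Reading the text**

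1. *Is the list closed?* No. The three signs follow the word for including, so they are examples.
2. *Is there an onset or drug-cause test?* Neither appears in the paragraph.
3. *Who classifies?* The investigator, who knows the arm. No blinded or independent classification is described.
4. *What brings events back?* A fatal or life-threatening event must be reported, which is a firm rule. The other route depends on the same investigator's view of expected severity, and no criterion is given.
5. *Does the SAE definition act as a backstop?* Not reliably, because it requires the investigator to believe the event was caused by trial treatment.
6. *Are the signs recorded elsewhere?* The paragraph says they usually are. The screening page of the case report form has tick boxes for the KD signs. The treatment, Day 5, week 6-8 and month 6 pages have no dedicated field for rash, eye redness or desquamation. An event filed as disease-related may leave no later trace.
7. *Can the analysis set help?* No. Analysing safety by intention to treat cannot restore events that were never recorded.

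**Size, as a hypothetical**

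The plan states no figure for this rule, so there is none to reproduce. The only planned input is the number per arm in section 3.6: 125 / 0.9 = 138.9, rounded up to 139. All AE rates and omission shares below are assumptions.

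Normal approximation, two-sided 0.05, with n = 139 per arm, recorded rates a and b, and m = (a + b)/2:

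power = Φ[(|a − b| − 1.96·SE0) / SE1], where SE0 = √(2m(1 − m)/n) and SE1 = √(a(1 − a)/n + b(1 − b)/n).

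*Equal omission, true 5% (test) and 15% (standard).*
- None left out: SE0 = √(2 × 0.10 × 0.90/139) = 0.0360 and SE1 = 0.0355. Power = Φ[(0.10 − 0.0705)/0.0355] = Φ(0.83) = 0.80.
- Half left out, so 2.5% and 7.5% are recorded: SE0 = 0.0261 and SE1 = 0.0260. Power = Φ[(0.05 − 0.0512)/0.0260] = Φ(−0.05) = 0.48.

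| Share left out in both arms | Power, true 5% vs 15% | Power, true 10% vs 20% |
|---|---|---|
| 0 | 0.80 | 0.65 |
| 25% | 0.66 | 0.51 |
| 50% | 0.48 | 0.35 |
| 75% | 0.26 | 0.19 |

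Exact calculation with Fisher's test for a rarer event agrees in direction: 10% (standard) vs 2% (test) gives 0.76, and halving both to 5% vs 1% gives 0.35.

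*Unequal omission.*
- Same true rate of 20% in both arms, with 25% left out in one and 50% in the other: recorded rates are 0.20 × 0.75 = 15% and 0.20 × 0.50 = 10%. The chance of p < 0.05 in that false direction is about 0.24, against a nominal 0.025. At true rates of 10% and 30% it is about 0.14 and 0.36.
- True 10% (test) and 20% (standard), with half left out in the standard arm only: the recorded rates are 10% and 0.20 × 0.50 = 10%, so the excess disappears.

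**The case against.** A reader might infer that the rule removes anything KD could explain. The text does not go that far, because the same paragraph restores events judged worse than anticipated and all fatal or life-threatening ones. The three examples also match KD entry signs, which suggests that the authors meant something narrow. That is a fair reading of intent, but the wording does not impose it.

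A reader might also infer that the rule hides the aspirin harms in section 2.1. The documents do not show this. Hepatic toxicity, gastritis, gastrointestinal bleeding, hearing loss and Reye's syndrome are not named as disease-related, and section 2.1 presents them as drug effects. The source cited for hearing loss is titled as associated with KD, but a title does not show how investigators would classify an event. The open wording permits omission of these harms and says no more than that. Anaemia is not in the section 2.1 list. It appears only in the title of the cited retrospective study.

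Some safeguards are real. CBC/DC and GOT/GPT are compared between arms as separate outcomes, measured at baseline, Day 5 and 6-8 weeks, so liver-enzyme and haemoglobin changes at those visits do not depend on attribution. An allergic reaction that leads to withdrawal has its own box on the exit form. Section 3.13 provides for an audit of AE reporting. None of these captures a rash filed as disease, and an auditor applying section 3.12 would accept that omission as compliant.

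Finally, any open-label trial carries some risk of differential AE labelling. That is true, and the figures above do not separate that background risk from what this rule adds.

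**Conclusion.** The point holds as a defect of wording with a consequence for a secondary objective. Section 3.12 contradicts its own AE definition, and it lets unblinded investigators leave out events on an open criterion with no onset or drug-cause test. The documented overlap is rash against allergic reaction to IVIG or aspirin. For the harms in section 2.1, omission is permitted but not directed, and the hepatic part is largely covered by the laboratory outcomes.

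The size and direction of any bias cannot be known from the documents. The power and error figures rest on assumed AE rates and assumed omission shares, and they show only that moderate omission would matter at 139 per arm. The coronary endpoint and the sample size are not affected. The change is worth making but is not critical.

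**What to change.** In section 3.12:

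1. Close the disease-related list to eye redness, rash and desquamation.
2. Record on the AE form, whatever the presumed cause, any rash that is new or changed after the first study dose and every event of a type named in section 2.1 (hepatic, gastrointestinal, hearing, Reye's syndrome). Mark suspected disease origin with a flag for possibly KD-related. The flag is an attribution and not a reason to omit.
3. Record expected desquamation and eye redness with the same flag, so that natural disease course stays identifiable and does not swamp the AE table.
4. Report AEs by arm with and without flagged events.
5. Tabulate worst CTCAE 4.03 grade by arm from the GOT/GPT and haemoglobin values already collected, without investigator attribution.

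The AE page in the case report form has columns for event, dates, intensity and treatment or comment, so the flag needs one added column. No visit, test or sample-size change is required. The cost is more low-grade AE entries in both arms. Whether a rash has changed remains an unblinded judgement, which is why both tabulations are needed. Section 3.12 also ends AE recording at hospital discharge, while the section 3.5 timeline marks AEs at 6-8 weeks. The two should be reconciled, because the flag cannot capture events that fall outside the recording window.

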### **Secondary objectives**

- To compare IVIG resistance rate, duration of fever after IVIG, duration of hospitalization, laboratory data (CBC/DC, GOT/GPT, and C-reactive protein (CRP)), Z score of coronary arteries, CAL at 6 months, adverse event (AE) and serious adverse event (SAE) between IVIG alone and IVIG plus high-dose aspirin as the primary therapy in acute stage of KD.

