#### Secondary outcomes

- **IVIG resistance rate:**

IVIG resistance is defined as persistent or recrudescent fever at least 48 hours but not longer than 7 days after completion of the first IVIG treatment.

- **Duration of fever after IVIG treatment**

We will record the body temperature every 6 hour during the hospitalization period.

- **Duration of hospitalization**

We will record the hospitalization duration from admission (or arriving emergency room) to discharge date.

- **Laboratory data**

Laboratory data of CBC/DC, GOT/GPT, and CRP will be checked at baseline, day 5, and 6-8 week.

- **Z score of coronary arteries**

We will estimate Z score of the proximal segments of LMCA, LAD, and RCA at baseline, Day 5, 6-8 weeks, and 6 month with 2D echocardiography. The calculation of Z score is based on the website of Taiwan Society of Pediatric Cardiology ([http://www.tspc.org.tw/service/z\\_score.asp](http://www.tspc.org.tw/service/z_score.asp)).

- **CAL rate at 6 months**

- **Adverse event (AE) and serious adverse event (SAE)**

We will record AE and SAE. Severity of AE will be based on Common Terminology Criteria for Adverse Events (CTCAE) version 4.03.

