### **3.11 Statistical methods**

All baseline characteristics will be used to investigate comparability of both trial arms. The primary outcome evaluation (CAL rate at 6-8 weeks) and secondary outcome of Z score of coronary arteries and CAL rate at 6 months will be performed on per-

protocol (PP) population while the other secondary outcome will be performed on intention-to-treat (ITT) population. Continuous variables will be described by using the mean (standard deviation) or median (interquartile range) as appropriate, categorical variables by using count (percentage). The participant characteristics will be compared using a  $\chi^2$  test for categorical variables, and a t test or Wilcoxon rank sum test for continuous variables. P values < 0.05 will be considered statistically significant.

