### **3.12 Adverse Events (AE) and Serious Adverse Events (SAE)**

#### **● Adverse Events**

An AE is any untoward medical occurrence in a subject during the participation of a clinical trial, regardless the possibility of a causal relationship. An AE can be any unfavorable signs or symptoms or diagnosed new diseases or deterioration of existing chronic or intermittent diseases. AEs will be collected after the participant has provided consent and enrolled in this clinical trial. If a subject experiences an AE after the informed consent document is signed but the subject has not started to receive treatment, the event will be reported as not related to the clinical trial.

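### Investigators who know the arm decide whether a raised Day 5 GOT/GPT is an adverse event, so any hepatic part of the AE comparison is open to uneven recording (minor; cheap improvement)

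*Combined protocol and SAP*

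**What the plan says.** Comparing "adverse event (AE) and serious adverse event (SAE) between IVIG alone and IVIG plus high-dose aspirin" is a secondary objective (protocol section 2.2). Section 2.1 gives the reason for interest: "serious aspirin side effects have been reported in children treated for KD, including hepatic toxicity, gastritis, upper gastrointestinal bleeding".

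Section 3.12 opens with a broad AE definition, covering any untoward occurrence whatever its cause, and continues: "An AE can be any unfavorable signs or symptoms or diagnosed new diseases or deterioration of existing chronic or intermittent diseases". Laboratory values are neither named nor ruled out. The disease-related-event paragraph then exempts what the natural course of KD can explain. It gives eye redness, rash and desquamation as examples, and states: "The disease-related events and conditions are usually recorded according to the protocol and should not be considered as an AE". An exempted event becomes an AE again if the investigator thinks it more severe than expected. On wording, the section adds: "It is the responsibility of the investigator to report AEs or SAEs by diagnosis terminologies, if possible".

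Section 3.9 states: "Participants and study investigators are unblinded to the group of IVIG alone or IVIG plus high-dose aspirin".

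Separately, section 3.4 makes the enzymes an outcome of their own: "Laboratory data of CBC/DC, GOT/GPT, and CRP will be checked at baseline, day 5, and 6-8 week". The case report form (CRF) records them as numbers. For continuous variables, section 3.11 says: "Continuous variables will be described by using the mean (standard deviation) or median (interquartile range) as appropriate". It analyses the laboratory and AE outcomes on the ITT population, and the SAP also puts the safety evaluation on ITT.

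**The concern.** Take a child whose GPT is raised at Day 5. Under section 3.12 one investigator may enter an AE, and another may judge that KD explains the value and enter nothing. No threshold, change-from-baseline rule or arm-independent assessment settles the matter. If that judgement were unrelated to treatment, it would only thin the count. Here the investigator knows whether the child is on high-dose aspirin. The value may be put down to aspirin in the standard arm and to KD in the IVIG-alone arm. Equally, a rise on aspirin may be passed over as expected.

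Drug toxicity is one of the two reasons section 2.1 gives for reassessing high-dose aspirin, so readers will look to the AE table for it. A difference there, or the lack of one, could reflect recording habits rather than the drug.

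**Working it through.** **The plan's own figure.** The documents give no figure for the AE comparison. The only stated calculation is the primary sample size, which reproduces at one-sided 5%: n = (1.645 + 0.842)² × (0.83×0.17 + 0.846×0.154) / (0.10 + 0.016)² = 125 per group; 125/0.9 = 139; 2 × 139 = 278. The present point does not touch it. It supplies n = 139 per arm for an ITT analysis.

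**Does any rule decide the classification?**
- *CTCAE v4.03* (sections 3.4 and 3.12) grades the severity of AEs. No text uses it to decide whether a value is an AE.
- *Auditing* (section 3.13) covers AE reporting under institutional regulations, not this classification.
- *The CRF AE table* has columns for event, dates, intensity and treatment or comment, but no laboratory criterion.
- *The laboratory comparison* does not depend on attribution, but it compares levels and does not alter the AE count.

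So the decision rests with the investigator.

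**Illustration of size.** The documents give neither the share of children with raised values nor the share recorded as AEs; both are assumed. Section 3.11 ties its χ² test to participant characteristics and names no hepatic-AE test, so a two-sided 5% χ² test is a further assumption.

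Recorded rate = true rate × share recorded. With a and b the recorded counts on IVIG alone and standard, p̄ = (a+b)/278 and X² = [(b−a)/139]² / [2p̄(1−p̄)/139], the chance of significance is the sum of Bin(a; 139, recorded rate on IVIG alone) × Bin(b; 139, recorded rate on standard) over all a, b with X² > 3.84.

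Chance of a significant difference when true rates are equal (%):

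| Share recorded, IVIG alone/standard | True 2% | 5% | 10% | 20% | 30% |
|---|---|---|---|---|---|
| All raised values, both arms | 4.5 | 4.8 | 4.8 | 4.9 | 5.0 |
| 50%/50% | 2.6 | 4.5 | 4.8 | 4.8 | 5.0 |
| 40%/60% | 3.4 | 7.2 | 11 | 19 | 29 |
| 30%/80% | 8.4 | 22 | 45 | 78 | 93 |

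A milder 45%/55% split gives 6.4-10.8% at true rates of 10-30%. With the shares reversed the percentages are the same and the false signal points against IVIG alone.

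In counts, a 20% true rate is 139 × 0.20 = 27.8 children per arm. At 40%/60% about 11.1 and 16.7 are recorded.

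**The other direction.** Suppose true rates are 10% on IVIG alone and 20% on standard, with 60% and 40% recorded. Recorded rates are then 6% and 8%, about 8.3 and 11.1 children instead of 13.9 and 27.8. By the normal approximation the chance of significance is about 10%, against about 65% if every raised value were counted. The 65% belongs to counting every raised value and does not carry over to a grade 2 or higher threshold, which would count fewer children.

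**The case against.** The strongest reply is that the hepatic question already has its own objective outcome. GOT and GPT are measured on a fixed schedule in both arms, recorded as numbers and compared on ITT. This stands. A reader might infer that the trial could miss, or wrongly report, liver toxicity altogether. The documents do not support that: a shift in enzyme levels remains detectable, and AE entries can be checked against the values.

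The AE definition is also wide enough to include a laboratory abnormality, and the request for diagnostic terms concerns naming and applies only where possible. Neither sentence removes enzyme values from AE reporting. The opening is the exemption that follows, with its non-exhaustive examples and its return route through investigator opinion.

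No passage says that KD raises GOT/GPT, and the three examples are outward signs. That weakens any prediction that investigators will use the exemption, but does not close it.

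Finally, the inputs are invented, and no hepatic-AE test is planned. Section 2.1 calls aspirin's risk low, and at low true rates the inflation is small: 40%/60% recording stays under the nominal 5% at a true rate of 2%. The 93% cell is an extreme corner and should not be quoted as an expected error rate.

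**Conclusion.** The point holds as a minor one. Section 3.12 leaves the AE status of a raised Day 5 GOT/GPT to investigators who know the arm, so any hepatic component of the AE comparison is open to differential recording in either direction. The primary endpoint and the GOT/GPT laboratory comparison are unaffected.

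The size cannot be derived from the documents. Under the assumed 40%/60% recording, false significance is about 3-7% at true rates of 2-5% and 11-29% at 10-30%; a rule applied alike to both arms stays at or below about 5%. These figures assume 139 per arm, equal true rates and a χ² test of hepatic AEs that the plan does not specify. They show what uneven recording could do, not that it will happen. The change is worth making because it is cheap and uses values already collected.

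**What to change.** In section 3.12 and the SAP:

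1. Derive CTCAE v4.03 grades by program for every recorded baseline and Day 5 GOT and GPT value, using site reference limits and without reference to arm or the investigator's attribution.
2. Report by arm, on the ITT population, the number and proportion worsening from baseline (all grade shifts, and grade 2 or higher), with risk difference and 95% CI.
3. Base the between-arm hepatotoxicity statement on this count together with the planned GOT/GPT comparison.
4. Keep investigator-reported hepatic AEs as a descriptive listing.
5. State that the disease-related-event exemption does not remove values from this tabulation.

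The gain is a count that does not depend on who attributes the rise; no power gain is claimed for the grade 2 or higher threshold. The cost is a short addition to each text and collection of site reference limits, with no new samples, visits or patients. Some rises not caused by treatment will be counted, but randomisation balances these between arms.
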